## Abstract

**Background:**

The COVID-19 pandemic disrupted life in extraordinary ways impacting health and daily mobility. Public transit provides a strategy to improve individual and population health through increased active travel and reduced vehicle dependency, while ensuring equitable access to jobs, healthcare, education, and mitigating climate change. However, health safety concerns during the COVID-19 pandemic eroded ridership, which could have longstanding negative consequences. Research is needed to understand how mobility and health change as the pandemic recedes and how transit investments impact health and equity outcomes.

**Methods:**

The TROLLEY (TRansit Opportunities for HeaLth, Livability, Exercise and EquitY) study will prospectively investigate a diverse cohort of university employees after the opening of a new light rail transit (LRT) line and the easing of campus COVID-19 restrictions. Participants are current staff who live either < 1 mile, 1–2 miles, or  > 2 miles from LRT, with equal distribution across economic and racial/ethnic strata. The primary aim is to assess change in physical activity, travel mode, and vehicle miles travelled using accelerometer and GPS devices. Equity outcomes include household transportation and health-related expenditures. Change in health outcomes, including depressive symptoms, stress, quality of life, body mass index and behavior change constructs related to transit use will be assessed via self-report. Pre-pandemic variables will be retrospectively collected. Participants will be measured at 3 times over 2 years of follow up. Longitudinal changes in outcomes will be assessed using multilevel mixed effects models. Analyses will evaluate whether proximity to LRT, sociodemographic, and environmental factors modify change in outcomes over time.

**Discussion:**

The TROLLEY study will utilize rigorous methods to advance our understanding of health, well-being, and equity-oriented outcomes of new LRT infrastructure through the COVID-19 recovery period, in a sample of demographically diverse adult workers whose employment location is accessed by new transit. Results will inform land use, transportation and health investments, and workplace interventions. Findings have the potential to elevate LRT as a public health priority and provide insight on how to ensure public transit meets the needs of vulnerable users and is more resilient in the face of future health pandemics.

**Trial registration:**

The TROLLEY study was registered at ClinicalTrials.gov (NCT04940481) June 17, 2021, and OSF Registries (10.17605/OSF.IO/PGEHU) June 24, 2021, prior to participant enrollment.

**Supplementary Information:**

The online version contains supplementary material available at 10.1186/s12889-022-13834-1.

## Background

Reducing health inequalities and harms from physical inactivity and air pollution are UN priorities [1, 2]. Public transit provides an opportunity to address these major challenges by increasing physical activity (PA) through active transportation (AT), mitigating greenhouse gas (GHG) emissions by decreasing vehicle miles traveled (VMT), and providing equitable access to jobs, education, and healthcare. Safe and accessible transit is critical for low-income groups. Essential workers comprise 26% of the working age population and 40% of transit riders in the U.S. [3], and nearly 50% are people of color [4, 5]. Given that more than 80% of the U.S. population lives in urban areas, LRT has potential to impact a majority of the population and to deliver numerous co-benefits [6, 7].

Sufficient PA is associated with reduced risk of numerous chronic conditions, including cardiovascular disease (CVD), type 2 diabetes, cancer, stroke, hypertension, and premature mortality [8–11]. Regular PA is additionally linked with improved well-being, fewer depressive symptoms [12], less stress [13–15], and improved quality of life (QoL) [16–19]. Despite known health benefits, fewer than half of U.S. adults meet the recommendation of 150 min/wk of PA [10, 11, 20, 21]. Additionally, there are PA disparities by income and race/ethnicity [22–28]. While the prevalence of sufficient leisure time PA is stable or increasing in white and college-educated populations, minority, less-educated and low-income groups are experiencing declines and have lower PA levels overall [29, 30]. Transit use often involves walking or biking to stations or destinations and is associated with more minutes of PA and meeting PA guidelines [31–38], providing an approach to combat physical inactivity [39–41]. Furthermore, promoting active transportation helps reduce greenhouse gas and traffic-related air pollution emissions which offers substantial co-benefits [42].

Americans in the lowest income quintile spend 1/3^rd^ of their income on transportation, a proportion that decreases as income rises [43]. These costs can impact spending on health-related expenses. Low-income households are more likely to have difficulty purchasing healthy foods [44, 45] and are less likely than higher-income households with similar health needs to access medical care [46]. Low-income households are expected to experience the greatest financial benefit from reducing the costs of vehicle ownership by replacing car trips with transit [47]. Evidence of the benefit of LRT access on employment status in low-income workers has been mixed [48, 49]. The Moving to Opportunity evaluation found that, while improved transit access was not associated with new employment, the odds of *maintaining* employment 4 to 7 years later was higher for those with better transit access [50, 51].

Transit ridership dropped sharply during COVID-19 due to health concerns. Studies have shown the greatest shift in travel mode was from public transit to private vehicles [52, 53]. The declines in transit use were smallest in communities with lower socioeconomic status and a higher proportion of essential workers [54, 55]. These findings highlight the vital role transit serves not only for essential workers, but for the greater population dependent on the essential services they provide [56].

The TROLLEY (TRansit Opportunities for HeaLth, Livability, Exercise and EquitY) study will prospectively quantify changes in multiple travel, health, and equity outcomes in a sample of diverse, adult workers following the opening of a new LRT line nearly two years into the COVID-19 pandemic. This research is uniquely generalizable within the post pandemic period. It further provides an advancement beyond prior LRT evaluations by recruiting employees who both live and work near rail stations [57]. The study provides a timely assessment of the impact of COVID-19 on transit use and perceptions and whether behaviors and health outcomes vary by socioeconomic and built environment factors.

## Methods/Design

### TROLLEY Study Design and Setting

TROLLEY is a prospective cohort study of 465 adults working at UC San Diego (UCSD) at 3 time points over 2 years of follow up. The new 11-mile UC San Diego Blue Line light rail extension opened in November 2021. This new line connected transit-served low-income and diverse communities in south and east San Diego County, where a large proportion of UCSD’s roughly 18,000 staff reside, to the major employment, education, and healthcare center of UCSD. The trolley line was completed prior to participant enrollment. However, data on travel, health and spending behaviors before COVID-19 and the LRT line opening will be collected retrospectively to allow for a pre-post comparison. UCSD is San Diego County’s second largest employer with a majority of staff from racial or ethnic minority groups and 90% filling non-managerial roles [58]. The new LRT line has three stops accessing the UCSD La Jolla campus and the VA and UCSD medical centers, providing a functional transportation option for university and healthcare workers. Unlike previous LRT intervention studies that recruited people around new stations that may or may not connect them with employment destinations [59–66], we will recruit staff who work near LRT and live either within 1 mile, 1–2 miles, or  > 2 miles from any San Diego LRT station. Previous research has long shown that environmental features at both home and work locations are significantly related with travel mode choice [67]. Therefore, the sampling design we proposed has greater potential to capture the impact on commute travel patterns.

The TROLLEY study framework, summarized in Fig. 1, is based on multilevel ecological models that highlight the many levels of influence on active living behaviors [68].

**Fig. 1 Fig1:**
[figure not shown]
TROLLEY Study Conceptual Model

Our study will assess selected variables at multiple ecological levels to understand how LRT access, demographics, perceptions/beliefs, travel demand programs, and built environment factors explain travel behaviors and, in turn, health and equity outcomes. Anticipated longer-term chronic disease impacts, shown elsewhere to be related with travel-related PA [69, 70], and downstream healthcare costs will not be assessed in this study due to the 2-year time frame.

The study was approved by UC San Diego’s Institutional Review Board prior to participant enrollment (Protocol #804110). All protocol modifications will be approved by the investigative team and submitted to the IRB. Participants consent to data being used in future analyses.

### Study Aims

The primary aim is to evaluate change in device-measured total and moderate-to-vigorous PA (MVPA), travel mode, and VMT. We expect minutes of MVPA and the proportion of AT (bike, walk, transit) trips, as a share of total trips, will increase. We also expect vehicle trips and VMT will decrease over time in those who live closest to LRT stations, compared to those who have less access to LRT.

### Equity aims

We will assess change in household expenditures, including transportation costs as a proportion of household income. We hypothesize the proportion of household income spent on transportation costs will decrease for those who utilize the new LRT, allowing for increased spending on health and QoL-related expenditures (i.e., healthy foods, medications, healthcare, etc.). We expect those with lower household income will have the largest decrease in transportation costs as a proportion of household income. We will additionally assess whether transit use is associated with an increase in the proportion of new UCSD hires from low-income areas and people of color, as well as potential impacts on employment continuity. 

### Secondary health aims

We will measure change in secondary health outcomes, including depressive symptoms, stress, QoL, and body mass index (BMI). We hypothesize those who use LRT will have fewer depressive symptoms, lower stress, greater QoL, and less weight gain over time than non-users.

### Transit and COVID-19 perception aims

We will evaluate transit-related intentions, benefits, barriers, social support, satisfaction, and self-efficacy in both transit riders and non-riders. We will track COVID-19 infection and vaccination status, and we expect transit and COVID-19 perceptions and infection/vaccination status to be independently related to LRT use.

### Subgroup analyses (effect modifiers)

We will examine whether change in outcomes over time is modified by distance to LRT, sociodemographic, and neighborhood environment (i.e., walkability) variables. We hypothesize those living closer to LRT stations, living in more walkable neighborhoods, or accessing more walkable stations, and low-income staff will improve their health and economic outcomes to a greater extent.

### Study sample and eligibility

Prior evaluations of new LRT have recruited people into treatment (exposed) and control groups based on distance from their homes to new rail stations [59–66]. There is debate on the degree to which LRT investments induce new transit ridership versus shifting existing users from bus to rail [57, 71–73]. The current study attempts to overcome this limitation by focusing recruitment on university staff who both live and work near the rail line. We are not recruiting students, given the longitudinal design, nor physicians/faculty, whose level of education and income would be higher than average and not generalizable to the broader population. Compared to faculty or students, UCSD staff live twice the average distance from campus, and roughly 50% live in areas accessed by transit [74]. To be eligible, participants must be 18 years of age or older, be a full or part-time employee at the UCSD La Jolla campus, have commuted to the La Jolla campus ≥ 2 days/wk prior to COVID-19 closures, have lived in the same location for at least 1 year with no plans to move, can walk without assistance, can read and write in English or Spanish, and spend most of their time in San Diego County. We aim to have equal distribution across distance to LRT groups (< 1 mile, 1–2 miles, > 2 miles), with 50% of the sample comprised by females, people of color, and low-income staff.

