**Fig. 2 Fig2:**
[figure not shown]
LRT stations with recruitment catchment areas MTS LRT stations (red), census block groups within one mile with at least 25% area overlap with station areas (green), block groups between one and two miles (white), block groups greater than 2 miles (no-LRT-group) with at least 25% area overlap with two-mile catchment areas (beige). Figure created by authors

The primary recruitment strategy is to identify interested and eligible staff through a pre-screening survey invitation sent by UCSD’s Department of Resource, Management and Planning, in both English and Spanish. The email was sent to > 17,000 active UCSD career staff, identified by their job title code. This method allows us to target staff specifically, exclusive of students and faculty. The email contains an embedded link to the study screener from our secure study database. Those who choose to complete the pre-screening survey provide their contact information, home address or nearest intersection, and answer the eligibility screening questions. The home addresses of staff who meet the initial screening criteria are then geocoded and spatially joined to the recruitment catchment buffers to determine which catchment area they live in. Those who are not eligible receive an email and a phone call explaining the reasons for ineligibility. Those who meet eligibility criteria are contacted by research staff who confirm interest and eligibility, answer questions, and obtain written informed consent.

In addition to university email, we are recruiting through UCSD staff distribution listservs and flyers, staff associations and unions, and on-campus advertising. These recruitment efforts target key UCSD units like Housing, Dining and Hospitality services, the Black, Chicanx/Latinx, and Pan-Asian Staff Associations, and hospital nursing and support staff groups to reach the intended population. Recruitment began in January 2022 and is ongoing, with 230 participants currently enrolled.

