### Data collection

Participants will complete a measurement visit after consenting to participation. Participants will be assessed 3 times during the 2 years they are enrolled in the study; once when first enrolled (2022), 1 year after enrollment (2023), and 2 years after enrollment (2024). All data collection will occur after the opening of the UCSD Blue Line Trolley. However, time 1 survey measures ask participants about commute, PA, and spending behaviors both at the time of assessment and, retrospectively, prior to the pandemic and the new LRT. The campus closure in March of 2020 due to COVID-19 provides a noteworthy reference point to aid recall. The UCSD Exercise and Physical Activity Resource Center (EPARC) distributes accelerometer and GPS devices and instructs participants how to wear the monitors. TROLLEY staff call participants during the wear week to ensure compliance. Links to the online surveys are emailed to participants, and participants receive a $50 gift card after completion of all assessments at each time point.

Study data are collected and managed using REDCap electronic data capture tools hosted at UC San Diego [79]. REDCap (Research Electronic Data Capture) is a secure, web-based application designed to support data capture for research studies, providing: 1) an intuitive interface for validated data entry; 2) audit trails for tracking data manipulation and export procedures; 3) automated export procedures for seamless data downloads to common statistical packages; and 4) procedures for importing data from external sources. Participants are assigned a study ID and all records are coded with the study ID rather than personal identifiers. All device data files will be kept on secure servers at the Social Sciences Computing Facility and data will only be accessible to investigators and project staff.

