### Covariates and effect modifiers

Sociodemographics include age, sex, race/ethnicity, education, marital status, annual household income, number of adults and children in the household, vehicle access, driving status, caretaking/childcare responsibilities, and years living at address. Health Status will be measured with a subset of the NHANES ‘medical conditions’ survey [104]. An 18-item questionnaire that measures reasons for moving to your neighborhood will be used to adjust for residential self-selection, which is a potential bias in environmental studies [105].

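### The one-year residence rule does not reach back to the pre-pandemic recall period, so recalled commute and spending can belong to a different home from the one that sets the distance group

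*Protocol article*

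**What the plan says.** **Residence.** Study sample and eligibility requires participants to "have lived in the same location for at least 1 year with no plans to move". The same sentence requires them to "have commuted to the La Jolla campus ≥ 2 days/wk prior to COVID-19 closures". Eligibility therefore reaches back before the pandemic for commuting, but not for residence.

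**Exposure.** Under Recruitment, the home address (or nearest intersection) given at screening is geocoded and matched to the catchment areas. This sets the distance group: under 1 mile, 1-2 miles, or over 2 miles from a trolley station.

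**Timing.** "Recruitment began in January 2022 and is ongoing, with 230 participants currently enrolled" (Recruitment). Data collection places the first assessment in 2022. The new line opened in November 2021 (TROLLEY Study Design and Setting), so every assessment follows the opening.

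**Recall.** Data collection states that "time 1 survey measures ask participants about commute, PA, and spending behaviors both at the time of assessment and, retrospectively, prior to the pandemic"; this recall period also precedes the line's opening. The section gives the anchor date as well: "The campus closure in March of 2020 due to COVID-19 provides a noteworthy reference point to aid recall". The purpose is given under TROLLEY Study Design and Setting: "data on travel, health and spending behaviors before COVID-19 and the LRT line opening will be collected retrospectively to allow for a pre-post comparison".

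**Tenure.** Covariates and effect modifiers lists, among the sociodemographics, "caretaking/childcare responsibilities, and years living at address". The article does not say that this item will be used to restrict or stratify the retrospective comparison.

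**The concern.** Three fixed elements of the design do not line up: how long the current home must have been held, the home that defines exposure, and the date to which recall is anchored. A participant can qualify, be placed in a distance group by the present address, and describe a commute and transport spending that started from a different address.

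For that person, the change from before the pandemic to time 1 contains the effect of moving house as well as whatever the line did. Recall is the only information the study has from before the opening. The Discussion concedes that pre-opening device data are lacking and relies on self-reported commute mode and frequency for insight into change. If people in one distance group moved more often than in another, or moved in ways that changed their commute differently, the retrospective comparison between groups would show a difference not caused by the line.

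**Working it through.** The article states no figure on this point to reproduce. The check is date arithmetic, followed by an illustration under an assumed move rate.

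**Inputs from the article**
- Recall anchor: March 2020 (Data collection).
- Residence required: 12 months before enrolment (Study sample and eligibility).
- Enrolment: from January 2022 (Recruitment), first assessment in 2022 (Data collection). December 2022 is taken as the latest month consistent with that schedule.
- Line opening: November 2021. Planned sample: 465.

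**Step 1: the uncovered gap**

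Gap = (enrolment month − 12 months) − March 2020.

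| Enrolment | Current home guaranteed from | Gap after March 2020 | Residence needed to reach March 2020 |
|---|---|---|---|
| January 2022 | January 2021 | 10 months | 22 months |
| June 2022 | June 2021 | 15 months | 27 months |
| December 2022 | December 2021 | 21 months | 33 months |

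The rule secures 12 months where 22 to 33 are needed. For a December 2022 enrollee, the guaranteed period begins one month after the line opened.

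**Step 2: how many could be affected**

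The documents give no move rate. With an assumed annual rate r, the share who moved in the gap is 1 − (1 − r)^(gap/12). For example, with r = 10% and a 21-month gap: 1 − 0.90^1.75 = 0.168.

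| Assumed r | 10-month gap | 15-month gap | 21-month gap |
|---|---|---|---|
| 5% | 4.2% | 6.2% | 8.6% |
| 10% | 8.4% | 12.3% | 16.8% |
| 15% | 12.7% | 18.4% | 24.8% |

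Applied to all 465, the extremes are 0.042 × 465 ≈ 19 and 0.248 × 465 ≈ 115. These are outer limits, because each treats the whole sample as having the same gap. Enrolment is spread out, and 230 were already enrolled when the article was written, so the true figure for a given r lies between the columns.

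**Step 3: what it does to the estimate**

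Let p be the share of movers in a distance group and d the mean change in the recalled outcome that the move itself caused among them. The group's mean change from before the pandemic to time 1 is shifted by p × d. The difference between groups 1 and 0 is shifted by p₁d₁ − p₀d₀. This is zero if moving is equally common and has the same mean effect in both groups; in general it is not zero otherwise. The documents give no values for p or d, so the size of the bias cannot be computed.

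**Step 4: do the planned methods remove it?**
- The random participant intercept absorbs stable differences between people, not a change of home within a person.
- Inverse probability weighting models membership of the current exposure group.
- The reasons-for-moving questionnaire adjusts for residential self-selection; it does not supply the earlier home.
- The limitations in the Discussion do not mention the mismatch.

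**The case against.** The strongest reply is that this leaves the main analysis alone. The primary outcomes are device-measured, the longitudinal model covers the three measurement time points, and all three follow the opening. That stands and limits the point to the retrospective comparison.

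A second reply is that the material for a remedy is already there: tenure is collected, a questionnaire on reasons for moving is planned, and covariates will be chosen with causal diagrams. An analysis-set definition could also sit in an analysis plan that is not shown. This stands in part. The affected participants can be identified, but the eligibility rule, the recall anchor and the address that sets exposure are all fixed in this article and do not agree.

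A third reply is that the size rests on an assumed move rate and that a move within the same distance band leaves the group unchanged. Both are true, although such a move can still change the commute.

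A reader might also infer more than the documents support:
- *That recalled vehicle miles travelled are affected.* Data collection names commute, physical activity and spending as recalled items; vehicle miles come from GPS and odometer readings. Only the general mention of travel in the design section could cover them.
- *That pre-period exposure to the new line is misclassified.* The extension did not exist before March 2020, so nobody had it, wherever they lived. The problem is a move confounded with the opening.
- *That the effect of moving outweighs the effect of the line.* The only expected effect stated is 3.46 min/day of physical activity; none is given for commute or cost.
- *That the one-year rule was meant to limit self-selection and fails at it.* The article gives no purpose for the rule.

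**Conclusion.** The point holds for the retrospective pre-post comparison and no further. By the article's own dates, residence is not guaranteed for the first 10 to 21 months after March 2020, and participants who moved in that window contribute recalled commute and spending from another home. Their change to time 1 combines a move with the opening of the line. Contrasts between distance groups are biased to the extent that moves, or their consequences, differ by group.

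Under assumed move rates of 5% to 15% a year, about 4-13% of the earliest and 9-25% of the latest enrollees would be affected. Those rates are an assumption, the constant annual rate is a simplification, and the direction and size of the bias are unknown. The device-measured analyses of times 1 to 3 are unaffected. The change is worth making because this is the study's only pre-opening contrast and the correction needs little.

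**What to change.** For any comparison that uses recalled pre-pandemic data, define the main analysis set as participants whose years at address show that they lived at the current home before March 2020. Report those who moved in later as a separate group, and give the full-sample result as a sensitivity analysis. Keep every participant in the analyses of times 1 to 3.

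One practical check is the resolution of the tenure item, which the article does not state. If it is recorded in whole years, two completed years (24 months) fall short of the 33 months needed by a December 2022 enrollee, while three (36 months) suffice for any 2022 enrolment. A move-in month would settle the cases in between.

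The cost is one analysis-set definition from a planned variable and a modest loss of numbers, confined to the retrospective comparison. Eligibility and recruitment need not change.
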